## Abstract

**Background:**

Parkinson’s disease (PD) is a neurodegenerative disease, for which no disease-modifying therapies exist. Preclinical and clinical evidence suggest that hypoxia-based therapy might have short- and long-term benefits in PD. We present the contours of the first study to assess the safety, feasibility and physiological and symptomatic impact of hypoxia-based therapy in individuals with PD.

**Methods/Design:**

In 20 individuals with PD, we will investigate the safety, tolerability and short-term symptomatic efficacy of continuous and intermittent hypoxia using individual, double-blind, randomized placebo-controlled N-of-1 trials. This design allows for dose finding and for including more individualized outcomes, as each individual serves as its own control. A wide range of exploratory outcomes is deployed, including the Movement Disorders Society Unified Parkinson’s Disease Rating scale (MDS-UPDRS) part III, Timed Up & Go Test, Mini Balance Evaluation Systems (MiniBES) test and wrist accelerometry. Also, self-reported impression of overall symptoms, motor and non-motor symptoms and urge to take dopaminergic medication will be assessed on a 10-point Likert scale. As part of a hypothesis-generating part of the study, we also deploy several exploratory outcomes to probe possible underlying mechanisms of action, including cortisol, erythropoietin and platelet-derived growth factor β. Efficacy will be assessed primarily by a Bayesian analysis.

**Discussion:**

This evaluation of hypoxia therapy could provide insight in novel pathways that may be pursued for PD treatment. This trial also serves as a proof of concept for deploying an N-of-1 design and for including individualized outcomes in PD research, as a basis for personalized treatment approaches.

**Trial registration:**

ClinicalTrials.gov Identifier: NCT05214287 (registered January 28, 2022).

**Supplementary Information:**

The online version contains supplementary material available at 10.1186/s12883-022-02770-7.

## Background

Parkinson’s disease (PD) currently affects 10 million people worldwide and its prevalence is projected to rise exponentially in the coming decades [1]. Several symptomatic treatments are available, the mainstay of which has been levodopa for over half a century. Many patients continue to experience significant disability, despite deployment of all available management strategies. Therefore, additional treatment modalities are needed.

Anecdotal evidence from individuals with PD suggests that ascending to high-altitude areas occasionally improves motor symptoms of PD, in a subacute way. These findings were recently confirmed in a survey that we conducted among individuals with PD who had recently been on vacation ([name] et al., manuscript submitted). We hypothesize that the positive effect of altitude on PD symptoms results from the decreased arterial oxygen tension at high altitude, which serves as an acute bodily stimulus for multisystem adaptations that potentially have protective effects on cellular homeostasis and survival [2, 3]. Therefore, altitude simulation has been the topic of research for potential therapeutic application in a variety of diseases.

Preclinical studies have suggested that hypoxia provokes release of survival-enhancing neurotransmitters. Specifically, the short-term clinical effects of hypoxia therapy appear to be related to augmented dopamine release from the substantia nigra [4–9]. Hypoxia therapy may improve parkinsonian symptoms via stabilization of hypoxia inducible factor 1 (HIF-1) and its downstream pathway, which in turn activates tyrosine hydroxylase (TH), the main rate-limiting enzyme in the production of dopamine [10, 11]. Several studies have demonstrated that HIF-1 stabilization leads to an increase in TH production, and consequently a rise in cellular dopamine content [8–13]. In addition, hypoxia protocols have a different influence on sympathetic nervous system activity, which regulates the body’s stress response [12, 14–16]. For example, long-term hypoxia increases noradrenalin-adrenalin ratio [12], which might ameliorate non-dopaminergic symptoms [17]. Taken together, these converging observations in animals and humans, provide a rationale that explains the potential positive effects of hypoxia on PD symptoms.

In addition to the short-term effects mentioned above, other studies also suggest that repeated exposure to hypoxia induces an evolutionary well-conserved adaptive mechanism. This adaptive response involves improves cellular energy metabolism as impaired by mitochondrial dysfunction, inhibits oxidative stress and induces adaptive plasticity, suggesting that in addition to the acute symptomatic effects, hypoxia might also exert long-term neuroprotective effects [18–20]. The concept behind these neuroprotective effects is the phenomenon of hypoxic preconditioning (HPC): induction of a sub-toxic hypoxic stimulus to improve the (systemic) tolerance of cells and tissues to subsequent more severe toxic stimuli. Although there is debate regarding the most potent hypoxia treatment regimen, clinical and preclinical evidence suggests that these effects are more pronounced when applied using a regime of intermittent hypoxia therapy (IHT) as compared to continuous hypoxia, meaning that hypoxia is present for short periods (i.e., minutes), interspersed with short periods of normoxic recovery. To date, hypoxia therapy, mostly IHT, has been used in a variety of populations, including fragile ones such as individuals with spinal cord injury, COPD, cardiac morbidity and multimorbidity, without any significant side effects [21–30]. However, the safety, feasibility and efficacy of hypoxia-based therapy have not been systematically investigated yet in individuals with PD. In this exploratory trial, we will assess the potential of hypoxia-based therapy in PD by assessing the physiological response to hypoxia, while also measuring the short-term symptomatic effects. To assess both continuous and intermittent hypoxia treatment regimens, this trial will deploy a double-blind, randomized placebo-controlled N-of-1 design, which allows for testing all selected hypoxia protocols in all participants [31].

### Study objectives

#### Primary objectives

(i) to
evaluate the safety and feasibility of both intermittent and continuous hypoxia
therapy in individuals with PD under well-controlled circumstances.

(ii) to explore the responsiveness of acute symptomatic outcome measures of
intermittent and continuous hypoxia therapy in individuals with PD under
well-controlled circumstances.

#### Secondary objectives

(iii) to assess the acute symptomatic effects on selected subjective and standardized symptom scales.

(iv) as a hypothesis-generating addition, to explore the potential mechanisms of (intermittent) hypoxia therapy on PD.

### Hypothesis

We hypothesize that short-term hypoxia-based protocols are safe to apply in individuals with PD without cardiorespiratory comorbidity, and that IHT has short-term effects on dopamine, noradrenalin and stress-responsive symptoms in PD.

## Methods/Design

### Multiple N-of-1 trials

In this study, we will conduct multiple series of randomized, double-blind and placebo-controlled N-of-1 trials (also known as single participant cross-over trials). This design includes the testing of multiple hypoxia protocols in every participant, and it allows for the analysis of treatment effects in the individual participant (in addition to group effects) because the participant serves as his or her own control. Lastly, this design can result in a higher power when considering small populations as compared to other traditional designs, making N-of-1 trials appropriate for studying rare diseases and personalized treatment [32, 33]. N-of-1 trials are especially suitable to investigate treatments in chronic, symptomatic conditions, where period effects (i.e. changes in disease state) and carry-over effects (i.e. lingering treatment effects) are limited. Given the slowly progressive nature of PD with relative stable symptoms, several N-of-1 trials have already been successfully performed to study symptomatic treatments in PD [34, 35].

### Study population

Twenty individuals with a diagnosis of PD (established by a neurologist according to the international Movement Disorder Society criteria) and Hoehn & Yahr stages between 1.5 and 3 will be included. Higher Hoehn & Yahr stages will be excluded for two reasons: firstly because of the significantly greater damage to dopaminergic pathways in advanced PD, which might limit the identification of nigrostriatal-mediated effects of hypoxia-based interventions; and secondly because of the high burden of testing participants in the OFF state in this more severely affected population. We aim to enrich our study population with individuals that have experienced (subjective) positive symptomatic effects at high altitude. In addition, we aim to include at least five individuals without prior experience with the positive effects of high altitude on their symptoms. This enrichment approach ensures that participants are more likely to be responders and allows us to validate our approach to identify each individual’s optimal protocol for clinical benefit. We believe that the selection bias introduced by our approach is justifiable because of the study’s explorative nature. In addition, PD is a very heterogeneous disease, for which a one-size-fits-all treatment approach is unlikely to be successful. Therefore, we wish to investigate for which individuals this therapy could be beneficial and the proposed approach is likely to be most promising. Main exclusion criteria relate to cardiorespiratory comorbidity and unstable PD medication. All inclusion and exclusion criteria can be found in Table 1.

**Table 1 Tab1:** Inclusion and exclusion criteria

Inclusion criteria	Exclusion criteria
Clinical diagnosis of Parkinson’s disease by a movement-disorder specialized neurologist	Individuals with diseases leading to restrictive and obstructive pulmonary diseases, pulmonary diffusion deficits, apnea and cardiac output deficits, such as pulmonary fibrosis, COPD, sleep apnea or excessive alcoholic intake, and congestive heart failure respectively
Hoehn and Yahr staging 1.5 to 3	Arterial blood gas abnormalities at screening day
Age > 18 years	Individuals with shortness of breath or other airway or breathing-related inconvenience related to lack of dopaminergic medication will be excluded
Participant can provide informed consent	Inability to comply to intervention in off-medication condition (for example due to extreme discomfort, distress or severe head tremor due to being OFF, i.e. without dopaminergic medication)
	Individuals with unstable dopaminergic medication dose (changes in the last month)
	Individuals likely to start dopaminergic treatment in the next month, also judged by their treating neurologist
	Individuals with active deep brain stimulation
	Individuals unable to provide informed consent

### Sample size

Because this is the first study in which the clinical effects of hypoxia therapy will be measured in PD and because of the study’s exploratory nature, a formal sample size calculation cannot be performed. A previously published power and sample size simulation study aggregated N-of-1 trials with multiple cycles of intervention and placebo per participant, and found that under certain assumptions N-of-1 trials needed only one-third of the sample size of an RCT to reach a similar power and type I error [36]. This was confirmed in a recent aggregated N-of-1 trial that investigated the effectiveness of the drug mexiletine in myotonia, in which the aggregated N-of-1 trial showed comparable treatments effects on a personalized Likert scale (i.e., the same outcome measure as we propose) with inclusion of 11 participants vs 57 participants in a traditional cross-over RCT [32]. Our proposed sample size of 20 was motivated by this work, in combination with the sample size consensus for feasibility studies of 20–30 [37].

The observed effect sizes and standard deviations of the different hypoxia protocols that are found to be clinically meaningful at the participant group level in this study (*N* = 20) will be used to simulate a power and sample size calculation for a future follow-up study that will be powered for efficacy using the data generated in this study.

### Recruitment, screening and inclusion

Individuals with PD will be recruited via the web-based ParkinsonNEXT recruitment website (www.parkinsonnext.nl) and, if necessary, from the outpatient registry of our university medical center – all patients on this list have already consented to be contacted for research purposes. After a first telephone contact with the coordinating investigator, potential participants will receive an email with detailed information about the study, including an overview of necessary time investment and the risks of participation, as well as the informed consent form. Specifically, we will ask participants with a positive altitude experience to share this project in their own networks of hikers or mountaineers.

Individuals will have a consultation by telephone conducted by the coordinating investigator to answer questions about the research and the informed consent. If the participant is still interested, screening questionnaires will be sent before the physical screening day. The coordinating investigator will contact the participant by phone to check if potential exclusion criteria are met, to prevent any unnecessary participant visits. This process will be registered in a pre-screening list. In this way, a transparent overview of study pre-selection will be available. The informed consent will be completed before initiation of the screening day. The participant has the right to withdraw consent at any moment during the study period. Drop-outs will be replaced.

### Intervention

We will study the response to multiple exposures of different pre-selected hypoxia protocols per participant, as at present there is no conclusive evidence for the effect of different hypoxia stimuli. This will optimize the chances for any changes in outcomes being identified, and allowing the possibility of defining the optimal dose of hypoxia as a therapeutic intervention individually. The selection of interventions was based on multiple studies that investigated and reviewed the hypoxia regimes that are currently perceived as being most effective [38–43]. In this N-of-1 trial design, every participant will receive two sets of five different conditions, with one being the placebo and the other four variants of an active intervention, consisting of either intermittent or continuous hypoxia at FiO2 0.127 (~ 4000 m) and 0.163 (~ 2000 m). All interventions are administered twice to enhance intra-individual discriminative power towards a sufficiently low or high probability (see *Statistical Analysis*). As it is shown that hypoxic preconditioning effects may linger for up to four days [44], a wash-out of at least five days between sessions will be built-in. Once a week, one of the following five conditions will be administered following the order resulting from a Latin square randomization (see *Statistical Analysis*):

Active interventions:Continuous hypoxia for 45 min, at ~ 2000 m (16.3% O_2_)Continuous hypoxia for 45 min, at ~ 4000 m (12.7% O_2_)Intermittent hypoxia with 5 × 5-min at ~ 2000 m (16.3% O_2_), interspersed with 5-min normoxic recoveryIntermittent hypoxia with 5 × 5-min at ~ 4000 m (12.7% O_2_), interspersed with 5-min normoxic recoveryPlacebo intervention:Continuous normoxia for 45 min (20.9% O_2_)

The intervention will be performed at Radboud university medical center in Nijmegen, the Netherlands. A commercially available hypoxicator will be used to deliver the hypoxic bout (*B-cat High Altitude*, the Netherlands). The hypoxicator (as an oxygen concentrator) is ISO 13485:2016 certified and uses a process called *pressure swing adsorption* to filter ambient air and to extract oxygen from that air. The principle is widely used in oxygen concentrators, but is inversely applied in the case of hypoxicators. Instead of oxygen-rich air, the resultant hypoxic gas is administered to the patient [45]. The hypoxicator is connected via medical-grade tubes to two large (> 50L) reservoir air bags that buffer the hypoxic gas mixture, which optimizes stability of the delivered FiO2. Intermittent hypoxia and the placebo situation is administered by switching a three-way Hans Rudolph® valve to either room air or the hypoxic circuitry. The intraday and between-day reliability of the hypoxicator were tested on multiple days before application in participants. Intraday variability was low (average range 0.2 percent points around desired FiO2) and between-day variability was within 0.1 percent points of desired FiO2. Seven days before the start of the first intervention, a one week at-home registration of self-reported outcomes of symptom severity will be conducted by a short daily morning survey. This assures a solid baseline of symptom severity that will be used in the Bayesian analysis (see *Statistical Analysis*).

#### Pilot phase

To ensure optimal safety, a pilot study of the first two participants selected for this study protocol will be deployed before conducting this study protocol at full pace. During the screening procedure, all individuals will be exposed to gradually decreasing FiO2’s until an FiO2 of 0.127 (~ 4000 m altitude) is reached. In these two individuals, the most intense intervention (continuous hypoxia at FiO2 0.127) will be administered for 45 min, to evaluate whether exhaustion in individuals with PD will limit the maximum safe duration as clinical experience is limited. In the remaining participants, the 4000 m intervention will be administered until ABG parameters have stabilized. When no serious adverse events occur, the protocol will be continued. During this pilot phase, the same stop criteria will be adopted as during the interventions.

#### Intervention

After completion of the screening day, participants will visit the hospital on a weekly basis, for 10 consecutive weeks. Treatments and in-hospital assessments will be conducted in the practically-defined OFF phase and will therefore commence in the morning. The treatment session in the OFF state is preceded by a baseline clinical assessment and is immediately followed by a post-intervention clinical assessment and an assessment after 30 min (Table 3). The intervention is administered in a hospital by an experienced lab technician, who also continuously monitors participants during and after the intervention. During the intervention, the inhaled FiO2 is measured continuously using the COSMED® metabolic system (*Quark CPET* metabolic cart for cardiopulmonary testing, COSMED Srl, The Metabolic Company, Italy), which also measures peripheral oxygen saturation, blood pressure, respiratory rate and tidal volume. In addition, the subjective participant experience regarding dizziness, discomfort and stress is registered by the lab technician during the intervention. In addition, to maximize safety of the participants during the intervention, clear stopping criteria are defined. If these are met, the lab technician will halt the intervention (‘Stopping Criteria’, Supplementary Materials).

### Randomization and blinding

#### Randomization

Subjects will be equally divided in 5 groups with different interventions order according to a Latin square design (5 periods/interventions). Allocation to intervention order will be randomized by a computer-generated randomization scheme. Interventions will be randomized at study start in two sets. As depicted in Fig. 1, set I will be randomized for the first five interventions and set II for the second five interventions. This reduces the risk of placebo effects in Set II potentially provoked by any positive effects that may have been experienced in Set I. This balanced randomization scheme minimizes bias introduces by the resulting order effect and period effect. Carry-over effects are minimized by ascertaining a sufficient wash-out period between every treatment.

**Fig. 1 Fig1:**
[figure not shown]
Design of the self-reported outcomes scoring in the multiple N-of-1 trials of every individual patient

#### Blinding

The intervention is double-blind for the participant and assessor, but not for the lab technician (because of safety and monitoring purposes). Ventilation during the administration is expected to increase by ~ 20%, mostly due to increased tidal volume and less often due to respiratory rate [46]. Risk of unblinding due to these limited ventilatory effects is unlikely and has not been reported in previous hypoxic experiments [28, 46–48]. Additionally, complaints of discomfort or shortness of breath are sometimes reported, regardless of the administered FiO2, indicating that this will not hamper blinding [23–25]. Changes in respiratory parameters will be available for the lab technician during the experiments, but will not be disclosed to the assessor. The assessor will only enter the lab after the intervention has been fully completed and will not have access to the vital parameters and blood parameters of the participant from which it might be possible to infer the assigned intervention. This problem is also mitigated by adding the placebo condition. We will assess the success of the blinding procedure by asking the participant in what sequence the different treatments were administered after the first and second treatment set.

### Outcomes and measurements

#### Primary outcomes

The main primary outcomes of this study are the safety and feasibility of IHT under well-controlled circumstances in a lab-based setting. Safety outcomes will be measured by the lab technician during the intervention and by the reporting of adverse events. The feasibility questionnaire (Supplementary Table 3) is designed together with a patient researcher. The questionnaire’s content is based on the main categories from a widely used feasibility framework [49]. Statements in every category (e.g. acceptability, expectancy) were subsequently inspired by previously published healthcare feasibility questionnaires. Primary outcomes are summarized in Table 2.

**Table 2 Tab2:** Primary outcomes

**Primary outcome variable**	*Measurement frequency*
Nature and number of adverse events	Every 10 min during intervention, up to one hour post-intervention, one time next morning post-intervention
Self-reported dizziness, discomfort and stress on a ten-point scale	Every 10 min up to one hour post-intervention, one time next morning post-intervention
Number of serious or irreversible adverse events	Every 10 min, up to one hour post-intervention, one time next morning post-intervention
	*Measured continuously for safety, recorded:*
- Blood pressure systolic-diastolic	Baseline and every 5 min—> 30 min post-intervention
- Heartrate	Baseline and every 5 min—> 30 min post-intervention
- Respiratory rate	Baseline and every 5 min—> 30 min post-intervention
- Oxygen saturation	Baseline and every 5 min—> 30 min post-intervention
Feasibility questionnaire (total score and subscores) (in *Supplementary Materials*)	After 1^st^, 5^th^ and 10^th^ intervention

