### Secondary outcomes

#### Self-reported outcomes

In this exploratory study, we will use a battery of outcomes to determine which symptoms or signs might respond to hypoxia. In accordance with accepted N-of-1 trial design recommendations and previously conducted trials [32, 50, 51], we have chosen to predefine personalized (self-reported) outcomes for each individual, scored on a 10-point Likert scale. Contrary to standardized PD scales, these outcomes better reflect important effects for the individual, and are potentially more sensitive to subtle treatment effects, reducing the risk of type II errors. Therefore, we included three participant-rated outcomes that assess on a 10-point Likert scale (allowing half points) general symptom impression, the urge to take a next dose of dopaminergic medication and the effect on one specific symptom that participants can choose themselves, based on goal attainment scale principles (Table 3). This symptom must fulfill the following criteria: it must fluctuate in severity throughout the day or between days, changes in its severity should be swiftly apparent and, if applicable, it is a symptom that previously improved at high altitude. To ensure a baseline score on these outcomes, participants will report these on a daily basis in the morning (in OFF) during the baseline period, i.e. 7 days preceding the start of the intervention period. On intervention days, participants will report these self-reported outcomes pre-intervention, directly post-intervention, 30 min post-intervention and from that moment on, another five times, on an hourly basis. In addition, these will be measured once every morning (i.e. in OFF) for the next three mornings after the intervention.

**Table 3 Tab3:** Secondary outcomes

Self-reported outcome variable	Researcher	Participant	Moment of measurement (in addition to baseline)	Measurement unit
**General symptom impression**		X	Directly after intervention and post-intervention 30 min, 1 h, 2 h, 3 h, 4 h and 5 h, and once every morning on the next three days	10-point Likert scale allowing half points
**Urge for dopaminergic medication** on the usual moments of intake		X	Directly after intervention and post-intervention 30 min, 1 h, 2 h, 3 h, 4 h and 5 h, and once every morning on the next three days	10-point Likert scale allowing half points

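### The 10-minute rating interval for dizziness, discomfort and stress equals the intermittent hypoxia cycle, so ratings in those sessions sit at one cycle position; scheduled adverse-event checks also stop before symptom scoring does

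*Protocol article*

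**What the plan says.** All references are to the protocol article.

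- **Ratings (Primary outcomes, Table 2).** Self-rated dizziness, discomfort and stress are a primary outcome, on a ten-point scale, scheduled "Every 10 min up to one hour post-intervention, one time next morning post-intervention". The section on the intervention under Study procedures confirms that the lab technician registers these three items while the session runs.
- **Adverse events (same table).** The schedule is "Every 10 min during intervention, up to one hour post-intervention, one time next morning post-intervention". The text above the table also names adverse-event reporting as a source of safety data and gives it no end date.
- **Vital signs (same table).** These are "Measured continuously for safety, recorded" as follows: "Baseline and every 5 min—> 30 min post-intervention".
- **Regimens (Methods/Design, Intervention).** Each intermittent protocol has five 5-minute hypoxic bouts separated by 5-minute normoxic recoveries. The two continuous hypoxia conditions and the placebo last 45 minutes. Each of the five conditions is given twice to each of 20 participants.
- **Follow-up of symptoms (Self-reported outcomes).** Symptom scores are collected each morning "for the next three mornings after the intervention".

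**The concern.** When a periodic exposure is sampled at an interval equal to its period, every sample lands on the same phase. The repeated ratings then describe one moment of the cycle, and adding more of them at the same spacing does not help. Continuous hypoxia and placebo have no cycle, so the same clock samples those sessions evenly. The primary tolerability ratings are therefore not taken alike in the two kinds of regimen.

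The primary objective covers the safety and feasibility of both intermittent and continuous hypoxia, and the article hopes to find each participant's optimal dose. Safety is to be analysed descriptively, so a reader will set the rating summaries of the protocols side by side. If the ratings sit at the end of recovery in one regimen and under hypoxia in the other, part of any difference may come from timing.

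The second issue is asymmetry of follow-up. Possible benefit is solicited on three mornings after a session, and possible harm on one.

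**Working it through.** **Inputs.** From the Intervention section: bout 5 min, recovery 5 min, 5 bouts, 20 participants, 2 intermittent protocols, 2 administrations. From Table 2: ratings every 10 min, vital signs every 5 min.

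**Session length.** 5 bouts × 5 min + 4 recoveries × 5 min = 25 + 20 = 45 min. This matches the stated length of the continuous and placebo sessions.

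**Cycle.** 5 + 5 = 10 min, equal to the rating interval. Hypoxia runs over minutes 0–5, 10–15, 20–25, 30–35 and 40–45. Normoxia runs over 5–10, 15–20, 25–30 and 35–40.

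**A 10-minute grid laid over that timeline, by minute of first rating:**

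| First rating (min) | In-session ratings (min) | Position in an intermittent session |
|---|---|---|
| 10 (clock from session start) | 10, 20, 30, 40 | all at the end of recovery, on the switch to hypoxia |
| 1 to 4 | e.g. 2, 12, 22, 32, 42 | all in hypoxia |
| 5 | 5, 15, 25, 35, 45 | all at the end of a hypoxic bout |
| 6 to 9 | e.g. 7.5, 17.5, 27.5, 37.5 | all in normoxia |

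Every row is locked to one position. In a continuous hypoxia session every row is rated under hypoxia.

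**Scale.** 20 × 2 × 2 = 80 intermittent sessions. On the session-start clock each has 4 in-session ratings, so 80 × 4 = 320 ratings share one cycle position.

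**Imprecise timing.** Minutes 10, 20, 30 and 40 are switch points. Assume each rating is off by an independent uniform error, with limits between ±0.5 and ±3 min. Then about 50% of ratings fall in each phase, and all four are normoxic in about 6% of sessions (0.5⁴ = 0.0625; simulated 6.0% to 6.4%). The lock is then broken, but Table 2 asks for no phase label, so the mixture could not be separated afterwards from scheduled times.

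**The 5-minute grid.** Minutes 5, 15, 25, 35 and 45 end the five hypoxic bouts, and minutes 10, 20, 30 and 40 end the four recoveries. That gives 9 readings, 5 hypoxic and 4 recovery, so both phases are covered.

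**Follow-up.** Scheduled adverse-event assessment covers one morning after the session and symptom scores cover three, which leaves two mornings on which only symptoms are solicited.

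**The case against.** **The phase is not stated.** A reader might infer that all in-session ratings under intermittent hypoxia are normoxic, that none of the 320 is taken during hypoxia, and that the intermittent protocols will look better tolerated. The article does not support this. It gives an interval and no first minute. A first rating at minutes 1 to 5 puts every rating in hypoxia or at the end of a bout, and even the session-start clock lands on switch points. This objection stands, and it leaves the direction of bias open. It does not remove the lock, because no fixed 10-minute clock samples both phases.

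**The exact minutes may be in Supplementary Fig. 1 or the full protocol.** Possibly, and neither is shown. A start minute given there would settle which phase is rated, but Table 2's interval would still reach only one.

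**The recall period is unstated.** If each rating covers the preceding 10 minutes, it includes a hypoxic bout and the lock matters much less. That is fair; the article does not say whether ratings are momentary.

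**Other safety data are sound.** The technician is someone "who also continuously monitors participants during and after the intervention", adverse events can be counted over intervals, and the 5-minute vital signs reach both phases. This stands. One might also infer that averaged saturation values are diluted by recovery readings, but the article specifies no session mean.

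**Later adverse events need not be missed.** Reporting has no stated end, and participants return weekly. The remark that "hypoxic preconditioning effects may linger for up to four days" concerns preconditioning and justifies the wash-out; it is not a stated duration of harm. What remains is only that scheduled solicitation of harm is shorter than that of symptoms.

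**No formal comparison is planned.** True; the effect is on description and on choosing between protocols, not on a test.

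**Conclusion.** The point holds in a limited form. The rating interval and the intermittent cycle are both 10 minutes, so on a fixed clock the in-session self-ratings in 80 sessions describe a single cycle position, while continuous sessions are rated under constant exposure. This follows from figures printed in the article.

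The size and sign of any bias cannot be derived. They depend on the start minute, on how strictly the clock is kept and on the recall period, none of which is given. If the clock counts from session start and ratings are momentary, discomfort under intermittent hypoxia could be understated; with a start at minutes 1 to 5 the ratings would describe only hypoxia or its end. The effect is confined to dizziness, discomfort and stress during the two intermittent protocols. The ratings in the hour afterwards follow one schedule in all conditions.

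On adverse events, scheduled assessment ends two mornings before symptom scoring does. That events would be lost is not shown. Both matters are worth correcting because they touch a primary outcome and the remedy is cheap.

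**What to change.** 1. In all five conditions, take the dizziness, discomfort and stress ratings every 5 minutes from minute 5 to minute 45, together with the vital signs already recorded. Keep the post-session schedule as it is. Using one clock for every condition keeps the sessions alike for the participant.
2. Label each rating and vital-sign reading with the scheduled gas phase. Because the 5-minute marks in intermittent sessions are switch points, state that the reading refers to the phase just ending, take it before the switch, and record the actual time.
3. Report intermittent sessions by phase, hypoxic and recovery separately. Moving the 10-minute clock to minutes 5, 15, 25, 35 and 45 instead would only lock it to the other phase.
4. Say whether each rating is momentary or covers the time since the last one.
5. Add one adverse-event item to the existing surveys on the second and third mornings, so that harm is solicited for as long as benefit.

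**Cost.** Against the session-start clock, 9 − 4 = 5 more short ratings per session, and one survey item on two mornings. No new visit or staff is needed. The drawback is a little more interruption during the session.
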